### Procedures

The standardization of the personnel who will participate in the study will be carried out in data collection, clinical assessment, and information processing. The procedures will be checked monthly, for quality purposes.

#### Children recruitment

Children will be recruited through contact with the TB control program of Medellín health authorities and other municipalities in the Metropolitan Area that agreed to participate. They will immediately supply the information on children under five years who are household contacts of pulmonary TB patients recently diagnosed and reported to the program. Health authorities’ staff will request authorization from children’s parents or guardians to share information with the research team and support in socializing the project to promote children's participation.

A nurse assistant (research staff) will collect data such as children's age, contact with a bacteriologically confirmed TB patient and the location by telephone contact. Additional information about the children and TB patients will also be collected at this moment. If the child's guardian is willing to participate in the study, an appointment is scheduled. Written informed consent signed by children´s parents or guardians will be required before any initial activities of the study.

#### First meeting

A general practitioner will perform a basic clinical assessment, including a complete interview and physical examination with emphasis on signs of active TB and the verification of the eligibility criteria. A trained health provider will apply the TST and obtain a blood sample (5 ml of venous blood) for the evaluation of interferon-gamma production (QuantiFERON®-TB Gold Plus-QFT Plus test). A TST reading will be performed after 72 h. Then, a chest X-ray will be performed to rule out the active disease with a standardized reading (two independent readers, with a standard form to fill in the information, and if there is disagreement, a third reader is involved to solve the discrepancy). Children with criteria for LTBI treatment will be invited to participate in the integrated care strategy. If the children’s parents or legal guardians do not want to continue the process, they will be referred to the primary healthcare facility within the health system.

#### Integrated care strategy

To guarantee treatment completion for LTBI with rifampicin for 4 months, the study will perform a strategy including six in-person assessments. The first five assessments are monthly, and the last one is in the twelfth month after recruitment. Additionally, two phone contacts are included, one 15 days after the beginning of the strategy and one at the eighth month. If needed, extra assessments could be scheduled. On the first assessment, the children will start the integrated care strategy, and they will receive care from a nursing assistant, a general practitioner, a pediatrician as needed, a nutritionist, a psychologist, and a social worker. The nutritionist assesses the child's nutritional status, anthropometric evaluation, eating habits and behaviors. Counseling is provided at the most convenient times to receive the medication and recommendations on fasting times. The psychologist performs a general assessment of the child's development, as well as an interview about family dynamics and parenting patterns to identify potential barriers or facilitators for parents or caregivers to adhere to the treatment scheme. The social worker will evaluate the children’s social, economic, housing conditions and family environment, as well as the social support network and other conditions that could lead to poor adherence to the therapeutic scheme. The social worker will also guide on government assistance routes in case situations of social vulnerability are identified. In this first meeting, the initial doses of rifampicin suspension are delivered, together with transport and food assistance. If at any point in the strategy, signs of physical or phycological abuse appear, the route of action stipulated by the Colombian authorities will be activated. The parents or legal guardians are instructed in the correct administration of the treatment, along with possible side effects. Then, at the monthly assessment, the general practitioner will evaluate the participants, recalculate the rifampicin dosage, supply the next doses, assess the adherence and side effects, and identify signs and symptoms of active TB. Liver function tests will be conducted during the second month of treatment. If during the in-person assessments or phone contacts, any child might have clinical or radiological criteria for active TB, an additional assessment will be scheduled, if indicated, induced sputum (two samples), aspirating gastric juice (two samples) and a single stool sample will be obtained. These samples will be processed for smear, liquid culture and Xpert MTB/RIF Ultra. In case of positivity for any of the samples, an evaluation for a pediatric infectious disease specialist will be performed, and the child will be referred to a primary healthcare facility to receive treatment for active TB. A private phone line will be available for the study to facilitate permanent communication with the parents or legal guardians and monthly monitoring. If any difficulty that could compromise treatment adherence is identified, the research staff (pediatrician, nutritionist, social worker, and psychologist) will perform additional assessments.

Unless it is strictly necessary or medically indicated, the parents or legal guardians will be exhorted to not give other medication or supplements to the children until the finalization of the four-month treatment scheme.

For children in the immunological window who started rifampicin treatment, TST will be performed two months later; if the result is still negative, treatment can be stopped according to clinical assessment. If TST turns positive, the fourth month of treatment should be completed.

### Outcomes

The primary outcome is treatment compliance, defined as the proportion of children who completed the treatment.

The secondary outcome is adverse events, defined as the proportion of children who presented any reaction during treatment.

### Operational hypothesis

The proportion of treatment compliance for latent TB in contact children with bacteriologically confirmed pulmonary TB patients in Medellín and the Metropolitan Area who receive the integrated care strategy is greater than the proportion of treatment compliance for children who received isoniazid in the 2015–2018 cohort.

### Data collection

Data are collected in a Microsoft Access application designed for the study, which is located on a secure server of the institution, with a personal identification number and a password for each member of the staff. The anthropometric measurements are collected in Anthro Software. The staff has a standardized procedure to collect the information. Every day, a staff member is responsible for double-checking the integrity and consistency of the data collected.

### Data analysis

To describe the characteristics of children's exposure to TB, a univariate analysis will be conducted, this will include the variables corresponding to the index case, the child's exposure, and other epidemiological variables.

Frequency distributions and proportions will be estimated to describe qualitative variables such as sex, socioeconomic stratum, affiliation to the health system, history of BCG vaccination, bacteriological study, and other variables.

The characteristics of the children in the 2015–2018 and 2020–2022 cohorts will be compared using the Z test for the difference in proportions for the qualitative variables and using the Mann‒Whitney U test for the quantitative variables according to the normality of those variables estimated with the Shapiro Wilk test. The characteristics of the index cases and children will be analyzed separately.

To examine the cellular immune response to *M. tuberculosis*, a univariate analysis will be performed. The proportion of response to the TST will be calculated according to categories in < 5 mm, between 5 and 9 mm and ≥ 10 mm, and the prevalence of positive response with a cut-off point ≥ 5 mm. The proportion of interferon-gamma production (QuantiFERON®-TB Gold Plus—QFT Plus) will be calculated according to the categories of positive and negative results.

The total agreement between the two immunological tests will be analyzed, as well as the different possibilities of discordance. The kappa index will also be calculated. The prevalence ratio of TST ≥ 5 mm and/or positive QFT will be calculated, and a bivariate analysis will be made with the characteristics of exposure to TB in children, adjusting for the index case cluster using Poisson regression. Subsequently, a multivariate analysis will be performed adjusting for the variables that met the Hosmer‒Lemeshow criterion in the bivariate analysis (*p*-value < 0.25).

A description of the latent TB treatment characteristics with a univariate analysis estimating proportions of qualitative variables related to administration of the treatment, side effects and treatment compliance (temporary or permanent suspension, cause of treatment suspension) will be made.

The difference in treatment compliance proportions between the 2015–2018 and 2020–2022 cohorts will be calculated, with 95% confidence.

The study timeline is outlined in Table 1.

**Table 1 Tab1:** Study timeline of enrolment, interventions, and assessments

Research activities	Study period							
	**Year 1**				**Year 2**			
	**Q1**	**Q2**	**Q3**	**Q4**	**Q1**	**Q2**	**Q3**	**Q4**
Training of study staff	X							

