## Methods

### Study design

This quasi-experimental study will compare the outcomes of the implementation of two treatment strategies for LTBI in children in Medellín and the Metropolitan Area (Valle de Aburrá), Antioquia, Colombia. The intervention cohort will receive an integrated care strategy, which consists of diagnostic tests, the supply of a scheme treatment with daily rifampicin for four months, active monitoring, permanent education and contact with the parents and/or guardians. In addition, social, psychological, and nutritional assistance will be provided, with a 12-month follow-up. The control group will be the historic 2015 to 2018 cohort who received the standard care protocol, with a 9-month scheme of isoniazid [24].

This protocol was conceived following the Standard Protocol Items: Recommendations for Interventional Trials (SPIRIT) guidelines [25] (supplement 1).

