### Study population

The population will be the children under five years who are household contacts of bacteriologically confirmed pulmonary TB patients from Medellín and the Metropolitan Area, notified to the surveillance system during 2021 and 2022, for whom LTBI treatment is indicated. The sampling method is nonprobabilistic since TB household contact children will be recruited as new cases (incidents) of smear-positive confirmed pulmonary TB appear in Medellín and the Metropolitan Area.

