### Sample size

According to previous studies, it is estimated that approximately 250 to 300 children who are household contacts of bacteriologically confirmed pulmonary TB patients from Medellín and the Metropolitan Area will be assessed for one year, with an estimated proportion of infection of 73.5%. The complete intervention of the integrated care strategy (with medication, incentives, and active follow-up) will be provided to children who require treatment for LTBI and who will also be selected incidentally, according to their willingness to participate. Considering the 59% isoniazid treatment adherence in the 2015–2018 cohort, adherence with the proposed strategy around 80%, 95% confidence, and 80% power, it is estimated that 75 children will be required in the proposed comprehensive care strategy (Epidat V 4.2). An additional 10% will be estimated due to lost to follow-up, therefore the total number of children to enter the integrated care strategy will be 85.

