Subsequently, in the same city of Colombia in 2012, a study was conducted on children under five years living with patients with bacillary pulmonary TB. It was found that 28.6% children who were contacted by telephone had been adequately studied (with chest X-ray and TST); for children who attended clinical evaluation, the prevalence of active TB was 7.9%, and only 19.4% received treatment for LTBI. Given that most of the household contact children were not adequately studied and therefore did not receive the indicated treatment, there was no significant impact on the decrease in the incidence of TB in these children with respect to the cohort study conducted between 2005 and 2009 [44].

Considering those findings, in 2015, a cohort study in Medellín, Bello and Itagüí, Colombia was started, with a before-after design and a two-year follow-up of children under five years of age who were household contacts of pulmonary TB patients to analyze the effectiveness of LTBI treatment with nine months of isoniazid as recommended by the national TB program, by comparison with children from a 2005–2009 cohort who did not receive treatment. The treatment cascade showed that from 329 children who met the inclusion criteria, 74% were assessed, 66% started treatment, 45% received LTBI treatment for at least six months, and 23.1% for nine months. The qualitative approach allows us to understand the complexity that underlies the effectiveness of LTBI treatment. This can be summarized in three categories: daily life and conditions of possibility for children exposed to TB and their families (including forced migration); the Colombian health system does not guarantee real access to TB diagnosis and treatment; and perceptions and social constructions around TB (TB remains as a stigma) [24]. Considering these findings, the research team proposed the present protocol study addressing some of the issues aiming to tackle the treatment completion barriers by an integrated care strategy for children exposed to TB.

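### The primary comparison with the historical cohort is a crude difference in proportions; no confounder adjustment is planned for compliance, although adjusted regression is planned for a secondary question

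*Protocol article*

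**What the plan says.** The Study design section of the protocol article calls the study quasi-experimental and names its comparator: "The control group will be the historic 2015 to 2018 cohort who received the standard care protocol, with a 9-month scheme of isoniazid". The Sample size section says that children needing LTBI treatment will receive the full strategy, and describes them as those "who will also be selected incidentally, according to their willingness to participate". The Eligibility criteria section excludes children whose families plan to move to a city outside the coverage area.

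The Outcomes section states: "The primary outcome is treatment compliance, defined as the proportion of children who completed the treatment". The operational hypothesis is that this proportion is greater under the integrated strategy than in the isoniazid cohort.

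The Data analysis section then contains three relevant elements:

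- **Baseline comparison.** "The characteristics of the children in the 2015–2018 and 2020–2022 cohorts will be compared using the Z test" for qualitative variables, with the Mann–Whitney test for quantitative ones. No use of the result is stated.
- **Adjusted modelling.** Poisson regression allowing for the index-case cluster, then a multivariable model with covariates chosen at p < 0.25. The outcome is TST and/or QFT positivity.
- **Primary outcome.** "The difference in treatment compliance proportions between the 2015–2018 and 2020–2022 cohorts will be calculated, with 95% confidence". No covariates, weighting, matching, stratification or clustering are attached.

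**The concern.** With a self-selected cohort and a historical control, confounding is the main threat to the primary claim. The protocol's own Discussion says that adherence is influenced by social aspects, migration and access to health services, and reports that forced migration and poor access underlay treatment effectiveness in the earlier cohort. If such factors are distributed differently in the two cohorts, a crude difference mixes them with the effect of the strategy. Testing for imbalance does not correct it.

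The stake is the study's single primary comparison. The Background section says that the data can contribute to national guidelines and support WHO guidance. A narrow interval around a confounded difference would look more secure than it is.

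**Working it through.** **1. The planning is also crude.** Inputs from the Sample size section: 59% against 80%, 95% confidence, 80% power. I take a two-sided 5% test with pooled variance and equal groups; the mean proportion is 0.695.

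n = [1.96 × √(2 × 0.695 × 0.305) + 0.842 × √(0.59 × 0.41 + 0.80 × 0.20)]² / 0.21² = [1.96 × 0.651 + 0.842 × 0.634]² / 0.0441 ≈ 74.3, so 75 per group.

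This matches the stated 75. An unadjusted two-proportion test is what the study was sized for.

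**2. Which differences between the cohorts the text supports.**

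- *Certain:* calendar period, 2015–2018 against a cohort whose recruitment began in July 2021.
- *Possible, municipalities:* the Discussion says of the earlier study that "a cohort study in Medellín, Bello and Itagüí, Colombia was started". The Children recruitment section takes Medellín and those other Metropolitan Area municipalities that agreed to take part, without listing them.
- *Possible, selection:* willingness to participate and the exclusion of families planning to move apply to the new cohort. The article does not say whether the historical cohort was filtered in the same way.

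**3. Size of bias under assumed inputs.** Bias = prevalence imbalance × effect on completion. Both inputs are assumptions.

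| Imbalance | Effect on completion | Bias | Share of planned 21 points |
|---|---|---|---|
| 10 points | 30 points | 3 points | 14% |
| 20 points | 30 points | 6 points | 29% |
| 30 points | 30 points | 9 points | 43% |

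**4. What this does to the test.** Suppose that the strategy has no effect, the historical rate is 59% and the bias favours the new cohort. The chance that a nominal two-sided 5% test favours the strategy should be 2.5%. The size of the historical analysis set is not stated. I use 75, and also 217, which is 66% of the 329 eligible children in the Discussion if 329 is the denominator (0.66 × 329 ≈ 217).

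| Bias | 75 v 75 | 217 v 75 |
|---|---|---|
| 3 points | 6% | 7% |
| 6 points | 11% | 14% |
| 9 points | 21% | 28% |

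**5. What the interval covers.** At 59% and 80%, the 95% half-width is 1.96 × √(0.59 × 0.41/n₁ + 0.80 × 0.20/75). This is 14 points with n₁ = 75 and 11 points with n₁ = 217. It reflects sampling error only.

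**6. How well the planned tests would flag imbalance.** Take 217 v 85 and prevalences centred on 50%. A 10-point imbalance is detected about 35% of the time and a 20-point imbalance about 88%. A 30-point imbalance (40% v 70%) gives z of about 4.7. Large imbalances would be seen; small ones often would not. In either case the plan states no consequence for the estimate.

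**The case against.** The strongest general objection is that an article condenses the protocol and adjustment may be left to an analysis plan. That does not answer this point. The Data analysis section gives a covariate-selection rule, a regression model and a cluster adjustment for the immunological question, and assigns the primary outcome a plain difference. The method is stated, not left out.

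Other objections stand and limit the point:

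- A reader might infer that the cohorts differ in index-case definition, pulmonary against bacteriologically confirmed. The text does not support this. The looser wording comes from a short summary of the earlier study, and the Intervention and Children recruitment sections use it for the new cohort too.
- A reader might infer that three municipalities are being compared with the whole Metropolitan Area. Recruitment is limited to municipalities that agreed, so the geographical difference is possible but not shown.
- A reader might infer that baseline tests on about 85 children would miss serious imbalances. That leaves out the historical children; step 6 shows that large imbalances would be visible.
- The bias figures are wholly assumed. The article gives no association between any covariate and completion and no prevalence difference between cohorts. The 30-by-30 pairing is extreme, and even that leaves 12 of the 21 points.
- Adjustment reaches only measured factors. It cannot remove period effects or unmeasured willingness, and cannot separate the drug regimen from the care package, because both change together. An adjusted interval would also not cover what is unmeasured.
- The sentence comparing the cohorts names no variables, so it is not known which covariates exist in both datasets.

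**Conclusion.** The point holds in this form: the primary estimate is crude in a historically controlled comparison entered by willingness, while adjusted, cluster-aware regression is reserved for a secondary question. That rests on the text alone. Calendar period is the one certain difference between the cohorts; municipality and selection are possible ones.

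The size is illustrative: 3 to 9 points of the planned 21 under the assumed inputs, with direction and true magnitude unknown. A reader might infer that the bias is known to favour the strategy, or that the planned 21-point effect is an artefact. The documents support neither. The historical cohort's entry filters are not described, and no covariate effects are given.

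**What to change.** Before the outcome comparison is run, specify the following:

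1. **Primary estimate:** an adjusted risk difference for completion, by regression standardisation or propensity weighting, with standard errors clustered on the index case.
2. **Covariates:** a pre-named baseline set confirmed to be recorded in both cohorts, for example age, sex, socioeconomic stratum, health-system affiliation and municipality.
3. **Overlap:** check it, and restrict to shared municipalities or strata where there are no historical controls, so that the model does not extrapolate.
4. **Balance:** judge it by standardised differences, not by p-values.
5. **Crude difference:** report it as supportive.
6. **Conclusion:** state that period effects and unmeasured willingness remain.

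The cost is analysis wording, a check of the historical dataset and some precision. If the covariates explain an assumed 10%, 20% or 30% of cohort membership, the effective size is n × (1 − R²). With 75 per group this is 67.5, 60 or 52.5, and power falls from 80% to about 76%, 71% or 65%. With about 217 historical children it falls from 93% to about 90%, 86% or 81%. Using every eligible historical child therefore recovers most of the loss. Restriction for overlap would reduce these numbers further, by an amount that cannot be worked out from the article.

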### Standard of care

The control group will be the historic 2015 to 2018 cohort of children with a diagnosis of LTBI who received a nine-month self-administered daily oral isoniazid scheme. The isoniazid comes in tablet form and must be diluted in water to be taken.

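### The primary compliance comparison has no term for index-case clustering, although the same section adjusts for it elsewhere; an unadjusted 95% interval would be too narrow

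*Protocol article*

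**What the plan says.** The Data analysis section gives one sentence to the primary comparison: "The difference in treatment compliance proportions between the 2015–2018 and 2020–2022 cohorts will be calculated, with 95% confidence". It names no interval method and no cluster term. Earlier in the same section, the bivariate analysis of positive TST and/or QFT against exposure characteristics is planned "adjusting for the index case cluster using Poisson regression". Clustering by index case is therefore recognised, but tied to that analysis only.

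The Sample size section starts from "Considering the 59% isoniazid treatment adherence in the 2015–2018 cohort" and "adherence with the proposed strategy around 80%, 95% confidence, and 80% power", and concludes that "it is estimated that 75 children will be required in the proposed comprehensive care strategy". It then states: "An additional 10% will be estimated due to lost to follow-up", which brings the total to 85. No design effect, allocation ratio or number of controls is given.

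On the comparator, Standard of care says: "The control group will be the historic 2015 to 2018 cohort of children with a diagnosis of LTBI". The Discussion gives that study's cascade: 329 children met the inclusion criteria, 74% were assessed and 66% started treatment.

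The Eligibility criteria admit every qualifying contact under five and set no limit of one child per index case. The Integrated care strategy section has parents or guardians instructed in giving the drug, a psychologist looking for family-level obstacles to adherence, and a social worker assessing housing, income and family environment.

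**The concern.** Children are found through index cases, so two or more may come from one home. The outcome, completion of a self-administered course in children under five, depends largely on what the household does. The article itself treats adherence that way, and its Discussion traces earlier non-completion to family life, migration, access to care and stigma. Positive correlation between children of one household is the natural expectation.

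With such correlation, the ordinary binomial variance of each proportion is too small. The 95% interval then covers less than 95%, and a test derived from it rejects too often. This is the study's only stated hypothesis, and its results are meant to inform national and WHO guidance. The authors made the adjustment for an exploratory analysis but did not name it for the comparison that carries the conclusion.

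**Working it through.** **Inputs from the article.** Control completion 0.59, intervention completion 0.80, 95% confidence, 80% power, and 75 children (Sample size). The 329 children and the cascade percentages come from the Discussion.

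**Inputs assumed.** Children per index case (m) and the ICC for completion are in neither the text nor the tables. I take m from 1.2 to 2 and ICC from 0.3 to 0.8, with the same design effect in both cohorts.

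**Step 1: reproduce the 75.** For two proportions, two-sided 5%, 1:1, pooled variance under the null and no continuity correction:

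n = [1.96·√(2·p̄(1−p̄)) + 0.8416·√(p₁(1−p₁) + p₂(1−p₂))]² / (p₂−p₁)², with p̄ = 0.695

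n = (1.2762 + 0.5335)² / 0.21² = 74.3, rounded up to 75.

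This matches exactly. A one-sided test gives 59, a two-sided test with continuity correction 84, and the unpooled form 72. The stated figure is thus the independent-observations, 1:1 number with a design effect of 1.

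**Step 2: design effect.** DE = 1 + (m − 1) × ICC.

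- m = 1.2, ICC 0.3: 1 + 0.2 × 0.3 = 1.06
- m = 1.5, ICC 0.5: 1 + 0.5 × 0.5 = 1.25
- m = 2, ICC 0.5: 1 + 1 × 0.5 = 1.50
- m = 2, ICC 0.8: 1 + 1 × 0.8 = 1.80

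**Step 3: effect on an unadjusted interval.** The correct width is √DE times the unadjusted width. The type I error of the unadjusted test is 2·[1 − Φ(1.96/√DE)].

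| DE | Correct interval wider by | Actual coverage | Type I error |
|---|---|---|---|
| 1.06 | 3% | 94.3% | 5.7% |
| 1.25 | 12% | 92.0% | 8.0% |
| 1.50 | 22% | 89.1% | 11.0% |
| 1.80 | 34% | 85.6% | 14.4% |

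These figures do not depend on the number of controls.

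**Step 4: number of historical controls.** If the 66% who started is a share of 329, there are 0.66 × 329 ≈ 217. If the percentages are chained, there are 329 × 0.74 × 0.66 ≈ 161.

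**Step 5: power at 0.80 v 0.59.** Each cohort size is divided by DE, with 75 children in the new cohort.

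| DE | 75 controls | 161 controls | 217 controls |
|---|---|---|---|
| 1.00 | 80% | 91% | 93% |
| 1.06 | 78% | 89% | 92% |
| 1.25 | 71% | 83% | 86% |
| 1.50 | 63% | 75% | 79% |
| 1.80 | 55% | 67% | 71% |

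On the 1:1 basis, power drops below 80% at a DE of about 1.01. With 161 controls it does so at about 1.35, and with 217 at about 1.46.

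**A caution on the 59%.** It does not follow directly from the cascade in the Discussion: 45/66 = 68%, 45/74 = 61%, 23.1/66 = 35%. All the power figures depend on which definition of completion lies behind it.

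**The case against.** **The sentence on the primary comparison fixes an estimand and a confidence level, not a variance estimator.** A condensed article may leave the estimator to an analysis plan. This stands in part: the article does not state a decision to ignore clustering. But it does name the cluster adjustment for one analysis and not for the other, so a reader following the text would leave the primary interval unadjusted.

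**A reader might infer that the study is underpowered.** The documents do not support that for the planned comparison. The 1:1 ratio is inferred from reproducing the 75, and the article states no per-group figure. Against 161 to 217 controls there is power to spare for a moderate design effect.

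**A reader might also infer that children of one index case share a caregiver, or that transport and food support is given per family.** The article says neither. It supports a shared household exposure and adherence driven by caregivers, which makes correlation likely but does not measure it.

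**The size may be small.** Only treated children count, about 85 of some 300 assessed, so the number per index case could be close to 1. That is why the range starts at 1.06.

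**The planned effect would survive.** At 80% v 59% and DE 1.8, the half-width is 1.96·√(1.8 × (0.59×0.41/n + 0.80×0.20/75)). That is 19.2 points with n = 75 controls and 15.0 with 217, so the interval around 21 points still excludes zero (about 1.8 to 40, or 6 to 36). This is correct for the planned effect, but a smaller observed difference would have less room.

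**Conclusion.** The point holds for the interval and not for power. As written, the primary comparison lacks the index-case adjustment that the same section applies elsewhere. With any positive within-household correlation and some households contributing more than one child, an unadjusted 95% interval is too narrow. The size is conditional on assumed values of m and ICC: 3% to 34% in width, and a type I error of about 5.7% to 14%, for design effects of 1.06 to 1.8.

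The sample-size figure makes no allowance for clustering, and on its own 1:1 basis almost any clustering takes power below 80%. Whether the actual comparison loses its stated power is open: it stays at or above 80% up to a design effect of about 1.35 (161 controls) or 1.46 (217 controls). More controls protect power but do not restore coverage. This should be fixed; it does not by itself threaten the study.

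**What to change.** State in Data analysis that the difference in completion will be estimated with index case as the cluster in both cohorts, by GEE with an identity link or by a risk difference with cluster-robust standard errors.

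First confirm that the 2015–2018 data hold an index-case identifier. The article shows that identifier in use only for the TST/QFT analysis. If it is missing for the historical children, say so and report how sensitive the interval is to an assumed design effect in that cohort.

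In Sample size, give the actual number of historical controls, the allocation ratio this implies, the assumed children per index case and ICC, and the resulting power.

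The cost is a few sentences, a check of the historical data and a somewhat wider interval. The point estimate need not change, and no additional recruitment follows from this point alone.
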